# Effect of transcutaneous auricular vagal nerve stimulation on the fatigue syndrome in patients with gastrointestinal cancers — FATIVA: a randomized, placebo-controlled pilot study protocol

**DOI:** 10.1186/s40814-023-01289-z

**Published:** 2023-04-22

**Keywords:** Cancer-related fatigue, Vagal nerve stimulation, Cytokines

## Abstract

**Background:**

Cancer-related fatigue (CRF) is defined as a “distressing, persistent, subjective sense of physical, emotional, and/or cognitive tiredness or exhaustion related to cancer or cancer treatment that is not proportional to recent activity and interferes with usual functioning.” CRF is frequently observed in cancer patients even before the initiation of tumor therapy. Its cause is not clear, but in addition to primary effects of therapy, a tumor-induced elevated level of inflammatory cytokines may play a role. Transcutaneous auricular vagal nerve stimulation (taVNS) is a noninvasive way to activate central nervous pathways and modulate pain perception and the immune system. It has positive effects on autoimmune conditions and can also improve fatigue associated with Sjogren’s syndrome. It is the main purpose of this feasibility study to investigate the feasibility of daily taVNS against CRF. Therefore, the stimulation protocol of the newly introduced smartphone app of the manufacturer is evaluated. Additionally, the effect taVNS on CRF and quality of life (QoL) shall be evaluated.

**Methods:**

Thirty adult patients with gastrointestinal tumors during or after treatment, relevant CRF (Hornheide questionnaire) and life expectancy > 1 year, are enrolled. Patients are randomized to treatment or sham arm and be informed that they will either feel the stimulation or not. Treatment group will receive left-sided tragus above-threshold stimulation with 25 Hz, 250 µs pulse width, and 28-s/32-s on/off paradigm for 4 h throughout the day for 4 weeks. Sham group will receive no stimulation via a nonfunctional electrode. A daily stimulation protocol with time and average intensity is automatically created by a smartphone app connected to the stimulator via Bluetooth®. Multidimensional Fatigue Inventory-20, Short-Form 36 and Beck Depression Inventory questionnaires will be filled out before and after 4 weeks of stimulation.

**Discussion:**

Primarily, the patients’ daily stimulation time and intensity will be evaluated through the electronic protocol after 4 weeks. Secondarily, the effect of taVNS on cancer-related fatigue and QoL will be measured through the questionnaires. As taVNS seems to modulate inflammatory cytokines, this noninvasive method may — if accepted by the patients — be a promising adjunct in the treatment of cancer-related fatigue.

**Trial registration:**

The study was approved by local ethics committee (21–7395) and registered at the DRKS database (DRKS00027481).

## Introduction

### Background

Fatigue is one of the most common short- and long-term side effects of cancer therapy. The National Comprehensive Cancer Network (NCCN) guidelines from 2015 define cancer-related fatigue (CRF) as “distressing, persistent, subjective sense of physical, emotional, and/or cognitive tiredness or exhaustion related to cancer or cancer treatment that is not proportional to recent activity and interferes with usual functioning” [1]. At the time of cancer diagnosis, up to 40% of patients complain of fatigue symptoms [2]. In the further course of therapy, more than 90% of patients suffer from cancer-related fatigue (CRF), which can be pronounced on a physical, emotional, and cognitive level. Common symptoms are tiredness, lack of strength and drive, concentration disorders, and a decreased quality of life (QoL), often associated with severe impairments in the private and professional performance. Fatigue can occur before, during, or after cancer treatment and can last for different lengths of time [1]. The 2-question test according to Whooles has become an accepted method to differentiate CRF from an underlying depressive disorder [3]. Even after the specific oncological therapy, up to 40% of all cancer patients continue to suffer from CRF, which greatly impairs their QoL [4]. The cause of CRF is multifactorial and not entirely elucidated yet. Therefore, a validated treatment concept does not yet exist. However, a chronic inflammatory process and an associated increase in inflammatory cytokines seem to play a role in the development of CRF [5]. In addition to their pro-inflammatory effects, both radiation and chemotherapy might have direct influence on the central nervous system and could contribute to CRF as well. Chemotherapy directly influences oligodendrocytes and neuronal stem cells and can therefore cause demyelination and vascular damage, especially in the context of neuroinflammation. One meta-analysis found a positive correlation between the severity of CRF and the concentration of inflammatory cytokine [6]. Thus, chronic inflammation appears to play an important role in the development of CRF.

A disbalance of the autonomic nervous system in favor of the sympathetic nervous system also seems to play a role [7, 8]. In this context, a dysregulation in the hypothalamic circuit [9], an alteration in the serotonergic system [10], and a disturbance in the sleep–wake cycle [11] could contribute to the development of CRF.

Invasive vagus nerve stimulation (iVNS) has been approved for the treatment of epilepsy since the late 1990s and depression since the early 2000s [12]. Its noninvasive variant, the transcutaneous auricular vagus nerve stimulation (taVNS), has been available for a few years and is based on the anatomical observation that one part of the ear — the tragus — is exclusively innervated by sensory fibers of the vagus nerve. Electrical stimulation of this area leads to activation of the brain comparable to the iVNS [13, 14]. taVNS has only few side effects, most notably skin irritation [15]. Via the “anti-inflammatory reflex loop,” taVNS leads to an anti-inflammatory effect, a reduction in inflammatory cytokines [16–18], and modulates cardiac vagal tone [19]. In the context of the current corona pandemic, it has also been observed in Covid-19 patients that taVNS reduces the inflammatory cytokine interleukin (IL) 6 [20]. In 2018, De Couck described the protective influence of the N. vagus on the prognosis of cancer patients [21] and encouraged the scientific society to perform further studies on the VNS in oncological patients [22]. This idea was taken up by Tibensky et al. in 2020, who discussed potential positive effects of the parasympathetic nervous system certain types of cancer (e.g., breast cancer), while prostate cancer, for example, may in theory be negatively influenced by an increased level of acetylcholine [23]. Furthermore, it has been observed that taVNS leads to an increase in heart rate variability (HRV) [24, 25] in patients with tinnitus. This observation may be important for cancer patients, since a reduced HRV is a predictive value for a poorer outcome [26, 27] and appears to be associated with CRF [7]. In summary, the stimulation of the vagal nerve has probably no positive effect on cancer patients by optimizing the actual cytostatic therapy. Instead, VNS has the potential to improve the quality of life — which has a significant impact on the survival of cancer patients — by reducing fatigue as a cancer- and cytostatic-specific side effect.

### Objectives

Based on the abovementioned observations that CRF might be caused by inflammatory processes which may be modulated by taVNS, it is the aim of this feasibility study to investigate whether daily taVNS is accepted by the patients as a treatment against CRF during this 4-week trial. Additionally, we will evaluate whether CRF can be influenced by left-sided taVNS. Established and sensitive questionnaires for depression, fatigue, und QoL will be used: Short-Form 36 (SF-36), Beck Depression Inventory (BDI), and Multidimensional Fatigue Inventory (MFI20). We chose this combination of questionnaires with respect to both the sensitivity for changes during taVNS and to the length and number of questions.

The SF36 questionnaire is established in many diseases. It is commonly applied in patients with fatigue [28, 29], autoimmune diseases [30, 31], Parkinson’s [32], and cancer [33–36]. It comprises 36 questions focusing on general aspects of QoL and will be applied to investigate the general wellbeing of our patients before and after taVNS. BDI examines the existence of depression and has already proven to respond to iVNS in epilepsy patients [37], to cervical noninvasive VNS in migraine patients [38], and to taVNS in patients with depression [39]. MFI20 is an established questionnaire in the assessment of cancer-related fatigue [40, 41]. Additionally, baseline values for a general population [42] and minimal clinically important differences are available [43, 44].

### Aim

It is the aim of the study to investigate whether 4 h of daily taVNS is accepted as a treatment against CRF and whether the symptoms of CRF and QoL can be influenced by taVNS in patients with gastrointestinal tumors and clinically apparent CRF.Primary endpoint: Acceptance of and compliance to taVNS, measured with the mean duration of taVNS per day. taVNS, is considered accepted when at least 80% of patients use the stimulator an average of at least 2 h per day.Secondary endpoint: Effect of taVNS on clinical scores (MFI20, BDI, and SF-36)

## Methods

The study will be performed at the University Medical Center Knappschaftskrankenhaus Bochum in cooperation with the University Medical Center St. Josef-Hospital, Bochum. Both hospitals belong to the University Medical Center of the Ruhr-University Bochum, Germany. The Department of Hematology, Oncology, and Palliative Medicine of the St. Josef-Hospital will identify, inform, and recruit the patients in its outpatient clinic and will transfer them to the Department of Neurosurgery at the Knappschaftskrankenhaus Bochum.

The attached SPIRIT table (Table 1) explains when the interventions and questionnaires will be performed within the study during enrolment, visit 0, and visit 1 (Table 1: Schedule of enrollment, intervention, and assessments).

**Table 1 Tab1:**
[figure not shown]
Schedule of enrollment, intervention, and assessments

### Patients

In accordance with the NCCN guidelines, all admitted patients of the Department of Haematology, Oncology and Palliative Medicine at the St. Josef-Hospital Bochum, who suffer from malignant gastrointestinal tumors, are routinely screened with a short CRF screening test (Hornheide’s questionnaire). If — before the initiation of an adjuvant therapy, a severity grade > 4 and a disability score > 5 are detected, eligible patients will be asked to participate in the study.

GDPR-compliant data collection will be pseudonymized in the eCRF of the university’s REDCap® system. The patients are automatically randomized by REDCap® into the stimulation or sham group (*n* = 15 each). Since the patients in the sham group will also be instructed in the use of the stimulator (which describes a tingling sensation of the stimulation in the ear), sham patients are told that they will receive a stimulation below the perception threshold. Since the rule “the more, the better” is not necessarily applicable in vagal nerve stimulation and a stimulation below the perception threshold could theoretically be effective, this procedure seems to be justifiable.

#### Inclusion criteria

Patients during or after therapy of a gastrointestinal tumorLife expectancy > 1 yearClinically relevant CRF (Hornheide’s questionnaire)Age > 18 years oldNo or stable depression for at least 4 weeks

#### Exclusion criteria

Severe psychiatric disease (e.g., schizophrenia) > 8 scores on NGASR suicidal questionnaireOngoing vagal nerve stimulation or s.p. vagotomyRelevant cardiac disease, e.g., bradycardic arrhythmia, insufficiency, and s.p. infarctionActive implant, e.g.. ICD, pacemaker, neurostimulator, cochlear implant, and VP shuntInability to understand the studyProgressive neurological disease (e.g., Parkinson’s, epilepsy, multiple sclerosis)PregnancyProstate carcinomaSkin disease like infection or eczema at the stimulation siteAnatomical anomaly at the stimulation siteOther severe condition preventing the successful participation in the study

#### Abort criteria

Occurrence of an exclusion criteriaOccurrence of severe cardiac arrhythmias

### Data logging

The patient is asked to download the manufacturer’s app available for Android and iOS, which connects to the stimulator via Bluetooth® and logs the stimulation time and average stimulation intensity per day. A cloud connection or a registration is not necessary. The app also shows the patient when the recommended total stimulation time of 4 h/day has been reached. Although the stimulator switches off after 4 h of continuous stimulation, there is no automatic blocking of the stimulator after 4 h of cumulative stimulation. This does not pose a problem as — according to the exclusion criteria — only patients who understand the study protocol will take part in the study. After 4 weeks, the respective data is exported from the patient’s smartphone and will be analyzed with respect to the mean daily stimulation time and mean daily stimulation intensity.

### Questionnaires

We will use 3 well-established questionnaires investigating QoL, depression, and fatigue: Short-Form 36 (SF-36, Beck Depression Inventory (BDI), and Multidimensional Fatigue Inventory (MFI20). These questions are digitally stored in the REDCap® system and will be filled out by our study nurses together with the patients. If a patient is unable to physically appear to the second visit, he/she will be given a temporary patient’s access to the respective REDCap® eCRF in order to fill out the missing questionnaires.

### Stimulation group

The device we use in this trial is the tVNS-L system manufactured by tVNS GmbH, Erlangen, Germany. It has a CE certificate for left-sided transcutaneous auricular vagal nerve stimulation with a fixed frequency of 25 Hz, pulse width of 250 µs, and 28-s on/32-s off protocol, and a variable stimulation intensity. It is an over-the-counter available system which can be bought in the manufacturer’s online shop. The stimulation will be performed at the tragus of the left ear in accordance with the CE certificate. The stimulation intensity is adjusted by the patient just above the perception threshold, until a light tingling is felt at the electrode. The stimulation shall be done for in total 4 h throughout the day, but not necessarily for 4 consecutive hours.

### Sham group

For stimulation in the sham group, the manufacturer offers a non-connected fake electrode which looks identical to the real electrode. Resistors within the electrode report a sufficient impedance to the stimulator so the control-LED of tVNS-L will always show good contact to the skin. The patient will be told that he/she is either in the group where he can feel the stimulation or in the group where the stimulation is below the threshold. The patients will therefore be blinded, the doctors won’t.

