### Sham intervention

The research version of tVNS (tVNS-R) with a variable set of stimulation parameters would have been scientifically more interesting, especially when it came to defining the sham group. However, the abovementioned legal issues encouraged us to use the CE-marked version tVNS-L with a fixed set of parameters and only variable stimulation intensity.

Defining the control/sham group has been discussed in literature. While some suggest stimulation of entirely different body areas [57], others chose the earlobe, which is not innervated by the vagal nerve, for control stimulation [58]. However, stimulation of the earlobe or other parts of the ear might cause interfering muscle activation [59, 60]. Interested and informed patients could also easily identify that they are in the control group by inserting the electrode “in a wrong” way. Therefore, we chose a fake electrode offered by the manufacturer with no electric connection between the stimulator and the patient.

In case the results indicate that a larger study could be feasible, we propose that future studies could consist of three groups of participants: the first group with a sham electrode, the second group with subthreshold stimulation, and the third with above-threshold stimulation. If there is no difference in the sub- and above-threshold stimulation (i.e., both show a similar effect), future studies could be limited to sham stimulation vs. subthreshold stimulation, therefore allowing a true blinded, even double-blinded, setting.

Another way to noninvasively stimulate the vagal nerve is via transcutaneous stimulation at the neck level. This device is called Gammacore® and delivers current through two skin electrodes. Sham stimulation can be performed by applying a fake stimulator which only delivers mechanical vibration instead of electric current. This method is used in a study which investigates transcutaneous VNS at the neck level against fatigue in lupus patients (NCT05315739). Another study investigates taVNS in a heterogenous group of patients with different types of cancer. The sham intervention is not exactly specified (NCT04563013).

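### Patients are called blinded although feeling or not feeling the current identifies their group; they are masked only to the sham delivering no current, so questionnaire contrasts can include a difference in expectation

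*Protocol article*

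**What the plan says.** All references are to the protocol article.

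- **Blinding claim** (Methods, Sham group): "The patients will therefore be blinded". The same sentence adds that the doctors are not.
- **What every patient is told** (same section): that "he/she is either in the group where he can feel the stimulation or in the group where the stimulation is below the threshold". The abstract's Methods paragraph agrees: patients will "be informed that they will either feel the stimulation or not".
- **What sham patients are told** (Methods, Patients): "sham patients are told that they will receive a stimulation below the perception threshold".
- **Sensation in the active arm** (Stimulation group): intensity is "adjusted by the patient just above the perception threshold, until a light tingling is felt at the electrode".
- **Sensation in the sham arm** (abstract and Sham group): the electrode is not connected, so no current reaches the patient. It looks the same as the real one, and the indicator light always shows good contact.
- **Endpoints and analysis** (Aim; Statistical analysis): effects on MFI20, BDI and SF-36 are secondary. Groups are compared by a difference in means or a Hodges-Lehmann shift, each with a 95% CI.
- **Later design** (Discussion, Sham intervention): a future comparison of sham with subthreshold stimulation is described as "therefore allowing a true blinded, even double-blinded, setting".

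**The concern.** The word *therefore* in the Sham group section draws blinding from a disclosure that removes it. A patient who knows that one group feels the current and the other does not needs only to switch the device on to learn which group applies. The Discussion reserves true blinding for a different, later design, which sits badly with an unqualified claim here.

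The scores at stake are self-reported fatigue, mood and quality of life, where what a patient expects can affect the answer. The Endpoints section says the findings will supply the sample size for a later trial and show which questionnaires respond best. If the arms differ in expectation, both choices could rest partly on that difference. A report that repeats the word *blinded* would give readers no reason to allow for it.

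**Working it through.** No figure in the plan is in dispute. The check is a side-by-side reading, followed by an illustration of size.

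**Step 1. Can the patient identify the group?**

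| | Active arm | Sham arm |
|---|---|---|
| Sensation by design | Tingling, set by the patient | None, no current |
| What the disclosure says this means | The group that feels it | The group below threshold |
| What remains hidden | Nothing about own treatment | That no current flows |

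The two descriptions given to patients map one-to-one onto the two arms, and sensation separates them. In principle all 30 patients can name their group in the terms they were given. The masking that remains concerns the nature of the sham, not group membership.

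**Step 2. Are the instructions consistent?** The abstract and the Sham group section describe a statement covering both possibilities. The Patients section, read literally, has staff tell sham patients which possibility is theirs. Under the first, the patient infers the group from sensation; under the second, staff announce it. The passages need to be reconciled.

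**Step 3. How large could the effect on the contrast be?**

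Inputs: 15 per arm (Justification of sample size); difference in means with a 95% CI, and no baseline adjustment described (Statistical analysis). Assumptions: all 30 patients contribute, with a common SD in both arms. The shift *b* is the difference in expectation effect between arms, in SD units; the documents give no value for it, so a range is shown.

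Half-width of the 95% CI, with 28 degrees of freedom:

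2.048 × √(2/15) = 2.048 × 0.365 = 0.75 SD

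Approximate chance that the 95% CI excludes zero when stimulation has no effect (normal approximation):

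Φ(b/√(2/15) − 1.96) + Φ(−b/√(2/15) − 1.96)

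| Assumed *b* (SD) | Share of half-width | Chance CI excludes zero |
|---|---|---|
| 0 | 0% | 5.0% |
| 0.2 | 0.2/0.75 = 27% | 8.5% |
| 0.3 | 0.3/0.75 = 40% | 13.0% |
| 0.5 | 0.5/0.75 = 67% | 27.8% |

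The last column describes how the interval would behave. The plan sets out no hypothesis test for the questionnaires.

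**The case against.** The strongest defence is that the masking is real, though partial, and that its limits were accepted for stated reasons. The electrode looks identical, the light shows good contact, and sham patients are not told that nothing is delivered. The Patients section argues that subthreshold stimulation might in theory work, so a sham patient may expect benefit too. The Regulatory considerations section explains why the device version with variable settings was practically ruled out, and the Sham intervention section gives reasons against an earlobe control. The remark about true blinding is largely the authors' own disclosure. The questionnaires are secondary endpoints in a feasibility study, reported as estimates with intervals.

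Most of this stands. It supports keeping the sham and treating the masking as partial. It also means that only the *difference* in expectation between arms enters the contrast, and the subthreshold explanation may reduce that difference. It does not make the unqualified word *blinded* correct, and it does not resolve the conflict between the Patients and Sham group sections.

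A reader might infer three stronger things that the documents do not support:

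- **That unblinded nurses rate the outcomes.** The questionnaires "will be filled out by our study nurses together with the patients", but only the doctors are said to be unblinded. The nurses' status is not given, and an article may leave it to the full protocol.
- **That the mode of collection biases the comparison.** Remote self-completion is a fallback for patients who cannot attend the second visit. It is open to both arms, and nothing ties it to allocation.
- **That the whole of any expectation effect falls on the contrast.** Expectation common to both arms cancels.

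**Conclusion.** The point holds. Patients are masked to the fact that the sham delivers no current. They are not masked to whether they belong to the group that feels stimulation, and the Sham group section claims more than that. The instruction to sham patients is also stated in two ways that do not agree.

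The consequence is confined to the between-arm contrasts in MFI20, BDI and SF-36 and to their use in planning a later trial; the point does not concern the primary endpoint. The size is unknown. An assumed differential shift of 0.2 to 0.5 SD would take up about 27% to 67% of a 0.75 SD half-width. This rests on an assumed shift, full follow-up at 15 per arm and an unadjusted comparison of means. It shows that such a shift would not be negligible beside the trial's precision. It does not show that a shift of that size will occur, and it would be wrong to conclude that the control is worthless.

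**What to change.** 1. **Restate the masking** in the Sham group section: replace *blinded* by *aware of felt versus not felt, unaware that the sham delivers no current*.
2. **Reconcile the Patients and Sham group sections** so that one neutral script covering both possibilities is used for every patient. This will not stop patients recognising their group by sensation, but it keeps staff from announcing it and makes the text consistent.
3. **Limit the conclusion** in the Statistical analysis and Endpoints sections: state that the questionnaire contrasts are exploratory, cannot separate stimulation from expectation, and should not by themselves set the effect size or the choice of questionnaire for the later trial.
4. **Add one short item** on believed treatment and expected benefit, asked soon after first use and reported by arm. The telephone call already planned after one week would serve. Asked only at four weeks, the answer would be mixed with perceived response.

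The cost is some rewording, one extra question and a more modest claim. Device, sham, sample size and primary endpoint stay as they are. The item would also show whether this sham is credible, which is useful for the three-group study that the Discussion proposes.
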